### Patient and public involvement

Patients and/or the public were not involved in the design, or conduct, or reporting, or dissemination plans of this research.

### Ethics and dissemination

The trial has been approved by the hospital’s medical ethics committee and has been registered with the Chinese Clinical Trials Registry, ChiCTR2100046050, ID. Written consent will be sought from each participant prior to the formal trial, and no names or identifying information of participants will be disclosed. In addition, all participants have the right to withdraw from the trial at any time without consequence. The study will start in February 2022 and is expected to be completed in December 2022.

The findings of this study will be disseminated through scientific journals, academic conferences, and university courses.

## Discussion

The burden of illness caused by depressive disorders is high, both in terms of personal distress, impaired social functioning and relationships, reduced quality of life, and socio-economic costs (56). Evidence from numerous studies shows that people with depression suffer from a social impairment, which in severe cases affects their normal work life (9). It is vital to improve the current situation of impaired interpersonal barriers in people with depression and to develop their social skills and abilities. Several of the currently available interventions for social functioning have certain shortcomings of their own, in addition to being insufficiently targeted. For example, IPT is mostly individualized and requires one-to-one interaction between the therapist and the patient, which can consume more human, material and financial resources; SST contains fewer entries, and the training of the patient is not yet comprehensive and still needs to be enriched; DIT is quite demanding for the therapist, requiring him/her to calmly analyze the self, immerse himself/herself in psychoanalytic therapy and always bear in mind the exploratory and analytical nature of the method (57).

The PEERS program was initially developed as an empirically supported social skills intervention program for young people with autism (35), involving both parents and peers (58). In the subsequent development of PEERS, many scholars have verified that the PEERS program has a positive impact on the improvement of patients’ depressive mood (32, 59, 60). In terms of improving social functioning, the PEERS program has the unique advantage of adding the involvement of parents, peers and a greater need for peer socialization among the youth population, increasing the motivation of the youth depressed population to participate. As the most specific stage in the development of depression, young people need to deal with different social partners, and psychological interventions and practical training for depressed people during this period can yield better results (16, 17). PEERS is delivered as a course, which reduces human and material resources and allows for timely practice of what is learned in the course, with the trainer simply guiding and the classroom being more patient-centered, making it simple, effective, and easy to implement. The PEERS program meets the needs of depressed young people for peer socialization and fills the gaps in several existing social functioning intervention programs.

Compared with foreign cultures, Chinese people are more introverted in emotional expression, and Chinese young people with depression are more difficult to express their feelings. The PEERS program proposed for this trial combines the national conditions of the country and the physical and mental characteristics of young people with depression. Localized PEERS training program has been constructed by experts to make the content more scientific, purposeful and relevant based on access to a large database and expert working sessions. The optimized PEERS program compensates for the shortcomings of several existing social skills training programs mentioned above, observes the clinical manifestations and signs and symptoms of young depressed patients, combines their physical and psychological characteristics, simulates a real social environment, and trains depressed patients in small groups, enabling participants to enhance interactive communication.

The design of the experiment took into account the possibility of changes in the subject’s condition, and thus we set a 20% lost visit to ensure an adequate sample size. The intervention course is arranged in four interlocking sessions to refresh the knowledge taught and apply it to practice, while arranging for the coaches to take the lead and ensure the course is conducted properly, but more so to encourage the hands-on practice by the patients, using the class as an opportunity for patients to communicate and learn from each other, promoting their understanding of each other and helping each other to practice their social skills.

Before the formal trial began, a pre-experiment was conducted to examine both the motivation and cooperation of the study subjects. At the same time, the content of the sessions was improved to make the program more relevant to the actual needs of young people with depression, based on the subjects’ self-specific feelings and evaluations. The pre-experiment followed strictly to inclusion and exclusion criteria for the selection of subjects and was randomized to prevent cross-contamination between subjects. We found that all study participants cooperated positively with the study, were highly compliant and were able to successfully complete all training sessions without dangerous negative emotions or side effects, validating the reliability and safety of the training in this study. After the pre-experiment, social anxiety scores, social avoidance and distress mood decreased in the intervention group compared to the control group, while social self-efficacy scores increased relatively after the intervention, as detailed in Table 3.

**TABLE 3 T3:** The grading of the pre-experiment (n1 = n2 = 6; LASA, Liebowitz social anxiety scale; SAD, social avoidance and distress scale; PSSE, scale of perceived social self-efficacy; HAMD-17, Hamilton depression scale).

Entries	Before the trial		After the trial	
	Intervention group	Control group	Intervention group	Control group
LSAS	55.50 ± 21.20	52.25 ± 20.30	41.75 ± 17.21	51.50 ± 13.90
SAD	22.50 ± 3.64	22.25 ± 3.90	16.25 ± 5.31	22.00 ± 4.30
PSSE	52.2 ± 10.35	43.75 ± 4.66	54.50 ± 7.92	45.00 ± 7.45
HAMD-17	19.25 ± 1.75	19.50 ± 1.19	10.75 ± 1.48	11.50 ± 2.06

If Chinese-specified PFEERS training is proven to improve depressed mood and enhance social skills in Chinese depressed youth populations, it could have significant implications for their recovery and prognosis. From a cross-diagnostic perspective, PEERS training may be a new time-saving and accessible method of training for health behavior change in other socially impaired populations, such as Chinese children with autism, youth with anxiety disorders, etc.

In conclusion, we hope that this study will provide evidence-based evidence for the application of PEERS training to the treatment of various types of socially impaired patients and provide a reference for the development of locally specific and targeted social skills training programs in each country.

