## Materials and methods and analysis

### Study design

This study protocol conforms to the Standard Protocol Items: Recommendations for Interventional Trials (SPIRIT) guidelines (see Additional file 1) and accords with the SPIRIT Figure (Figure 1). The proposed PEERS training for the trial is based on literature research and expert discussion and is an optimized update of the original PEERS training program. Participant engagement in the trial will be divided into two phases, a non-intervention phase before randomization and an intervention phase 6 weeks after randomization. This trial was designed to validate the efficacy of the localized PEERS training, and therefore the control group in this trial will not receive any interventions other than usual care. Participants will be randomized by ward to receive the intervention, and due to the specific nature of the intervention, blinding will not apply to the interventionists, and the study will remain blind to scale assessors and data entry only.

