### Participants

Trial participants were recruited from young adults with depression attending a specialist mental health hospital in Huzhou from July 2022 to January 2023. It is the largest specialist mental health hospital in the region, with psychological and psychiatric disorders diagnosis and treatment as its specialty, treating people with all types of psychosomatic disorders, with a wide range of influences and strong representation.

The purpose, procedures, possible risks, benefits, and other information about this trial will be explained in detail to participants. The trial participant schedule is specified in Figure 2.

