### Assignment of intervention

Prior to the start of the intervention, different ward were randomly divided into intervention and control groups using a coin toss by an investigator not involved in the implementation of the intervention to prevent contamination, and eligible subjects were sought within the respective ward.

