### Statistical analysis

#### Statistical data collection

The HAMD-17 scale will be administered by a professional psychologist, while the remaining LSAS, SAD, and PSSE scales will be completed on the spot by the assessor who will carefully explain the purpose of the study and the method of completion to the study participants and gain the support and understanding of the patients before completing the questionnaire. The scale assessors will be selected from those who do not perform clinical interventions to reduce bias due to subjective factors. A paper version of the questionnaire is given to inpatients, and patients are followed up by phone or text messages after they are discharged from the hospital. When all the scales have been collected, the information is promptly reviewed and confirmed, and patients are asked to cooperate in correcting any problems found.

Data entry will be carried out by investigators who are not involved in the implementation of the intervention. After the data has been safely collected and entered, the data collected will be statistically analyzed with SPSS 25.0. *P* < 0.05 means the differences are statistically significant.

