### Statistical methods

For baseline comparisons, age, LSAS scores, SAD scores, PSSE scores, and total HAMD-17 scores are measurement data for both two groups and will be statistically described using the mean ± S.D., with Paired Sample *T*-Test used to assess between-group balance. The general profile of the test subjects, including gender, education level, occupation, marital status, mode of payment for medical care, per capita household income, type of depression, duration of illness, type of medication, family history, and past history, are all categorical data that will be statistically described using frequencies and percentages, and chi-square tests to assess between-group balance.

The primary outcome indicators (LSAS scores at week 3 and week 6 post-intervention for two groups of patients) and secondary outcome indicators (SAD, PSSE, HAMD-17 scores at week 3 and week 6 post-intervention for two groups of patients) will be compared using Repeated Measures ANOVA to analyze the efficacy of PEERS training at different time periods. Considering the possible interaction between intervention and time, we choose Simple Effects to analyze the different effects of different time variances on PEERS training.

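### PEERS is taught in small groups in one arm only, but the named Repeated Measures ANOVA treats patients as independent, so any positive class correlation makes its error bars too narrow

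*Protocol article*

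**What the plan says.** - **Group delivery.** The Discussion says that the optimised programme "trains depressed patients in small groups, enabling participants to enhance interactive communication". It also describes the course as "using the class as an opportunity for patients to communicate and learn from each other". Mutual influence within a class is therefore an intended part of the treatment.
- **Control arm.** Under Study design, "the control group in this trial will not receive any interventions other than usual care". Table 1 lists the content of usual care and contains no group classes.
- **Allocation.** Under Assignment of intervention, "different ward were randomly divided into intervention and control groups using a coin toss", and "eligible subjects were sought within the respective ward". The number of wards is not stated.
- **Analysis.** Under Statistical methods, the LSAS scores and the SAD, PSSE and HAMD-17 scores "will be compared using Repeated Measures ANOVA to analyze the efficacy of PEERS training at different time periods", followed by simple effects. No class or ward term is named.
- **Sample size.** The Official experiment section uses a variance of 243.04, a squared difference of 272.25, alpha 0.05 and beta 0.10. It arrives at 62 patients, raised to 74 (37 per arm) for loss to follow-up, with no allowance for correlated patients.

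The document gives neither the size of a class nor whether a class may mix patients from several wards.

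**The concern.** Patients in one class share trainers, companions and group dynamics, and practise on each other. Their outcomes can be expected to resemble each other more than those of patients in different classes. The between-group part of the planned ANOVA assumes independent patients with equal variance in both arms. Class delivery can break both assumptions, and only under PEERS.

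This differs from the correlation due to allocating wards, which affects both arms and which the ANOVA also ignores. Class correlation is produced by the treatment. A sponsor who later corrects for ward may or may not have dealt with it, depending on how classes are formed.

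At stake are confidence intervals that are too narrow and too many false positive results on the primary outcome and the three secondary scales. The protocol fixes the method, so this is an objection to a stated choice and not to a detail left for an analysis plan.

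**Working it through.** **1. Inputs from the protocol.** SD = √243.04 = 15.59. Difference = √272.25 = 16.5. N = 62, taken as 31 per arm before the allowance for loss.

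**2. The plan's own figure.** The printed formula is 4(z_α + z_β)²σ²/δ².
- One-sided alpha: 4 × (1.645 + 1.282)² × 243.04/272.25 = 30.6, so 31.
- Two-sided alpha: 37.5, so 38.

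The stated 62 is matched only if the one-sided 31 is read as per arm and doubled. 62 × 1.2 = 74.4, given as 74. No term for clustering enters.

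**3. Effect of classes in one arm.** For class size m, the PEERS-arm variance inflation is DE = 1 + (m − 1) × ICC; for controls it is 1. The ratio of true to assumed standard error of the difference is r = √((1 + DE)/2). The type I error of the nominal 5% test is 2(1 − Φ(1.96/r)). Class size and ICC are assumptions. The last column is power at the protocol's inputs, Φ(16.5/SE − 1.96), with SE = 15.59 × √(2/31) × r = 3.96 × r.

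| m | ICC | DE | r | Type I error | Power |
|---|---|---|---|---|---|
| any | 0 | 1.00 | 1.000 | 5.0% | 98.6% |
| 3 | 0.05 | 1.10 | 1.025 | 5.6% | 98.2% |
| 4 | 0.05 | 1.15 | 1.037 | 5.9% | 98.0% |
| 6 | 0.01 | 1.05 | 1.012 | 5.3% | 98.4% |
| 6 | 0.05 | 1.25 | 1.061 | 6.5% | 97.6% |
| 6 | 0.10 | 1.50 | 1.118 | 8.0% | 96.1% |
| 6 | 0.15 | 1.75 | 1.173 | 9.5% | 94.4% |
| 8 | 0.05 | 1.35 | 1.084 | 7.1% | 97.0% |
| 8 | 0.10 | 1.70 | 1.162 | 9.2% | 94.8% |
| 8 | 0.15 | 2.05 | 1.235 | 11.2% | 92.1% |

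**4. Check by simulation.** Two-sample comparison, 31 per arm, classes in the PEERS arm only, 40,000 runs per setting:
- ICC 0: 5.0%.
- Classes of 6 to 7: 6.5% at ICC 0.05 and 8.1% at ICC 0.10.
- Classes of 7 to 8: 6.8% and 9.0%.

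These agree with the formula.

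**5. Would a ward correction remove it?** Simulated t-test on ward means, assuming 36 per arm, 2 or 3 wards per arm, six classes of six, class ICC 0.05 to 0.15 and no ward effect. Type I error is about 5% if every class sits inside one ward, and about 6 to 8% if classes mix the wards evenly.

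**6. Limits.** Steps 3 and 4 treat one time point. That is closest to the planned simple-effects comparison at week 3 or week 6, and it stands in for the full repeated-measures test.

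**The case against.** **The size is assumed.** This stands. The documents support neither a class size nor an ICC, and with very small classes or an ICC near 0.01 almost nothing is lost. What does not depend on the assumptions is the direction: with any positive class ICC, the named analysis understates the standard error.

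**Lost power.** A reader might start from a nominal 90% and infer a fall to about 75 to 86%. The protocol's inputs do not support that. With 31 per arm and a difference of 16.5, two-sided power is 98.6% for independent patients and 92 to 98% over classes of 6 to 8 and ICC 0.05 to 0.15, by the normal approximation. One caution applies. With Satterthwaite degrees of freedom for four or five classes (about 6.5 to 12), the same range gives 95% down to 81%. It falls below 90% at ICC 0.15, and at ICC 0.10 with classes of 8. That reflects how few classes there are and is not enough to claim that the stated power is missed.

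**Classes must mix wards.** A reader might infer this from recruitment "from July 2022 to January 2023": 37/7 = 5.3 PEERS patients a month, so with 2 or 3 PEERS wards one ward would need 2.3 to 3.4 months to fill a class of six. Both the ward count and the class size are assumed. With a single PEERS ward, 6/5.3 = 1.1 months is enough. The Ethics and dissemination section also gives other study dates (February to December 2022). Patients were sought ward by ward and wards were allocated to prevent contamination, so ward-based classes are at least as natural a reading. Mixing is only a possibility that the text leaves open.

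**Rolling classes.** Successive or rolling classes inside one ward might seem to escape a ward-level analysis. They do not, because they remain nested in that ward.

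**Overlap with ward clustering.** The ANOVA has no ward term either, and that affects both arms. The class point is separate, but if classes are nested in wards a ward-level analysis deals with both.

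**Conclusion.** The point holds as a defect of the named analysis. PEERS is delivered in groups in one arm, and the Repeated Measures ANOVA takes no account of it, so with a positive class ICC the PEERS-arm standard error is too small for all four scales. Under the assumed classes of 6 to 8 and ICC 0.05 to 0.15, this means a 6 to 24% understatement relative to the assumed standard error and a type I error roughly 1.5 to 6 percentage points above nominal. Smaller classes or a weaker correlation make it minor. The harm claimed is excess false positives and narrow intervals, not a shortfall from 90% power. Whether it would survive a correction for ward depends on how classes are formed, which the document does not say. It should be corrected, and the correction is modest.

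**What to change.** - **Record and state.** Record the training class of every PEERS patient from the start, since it may be hard to reconstruct later. State whether classes are kept within wards.
- **Model.** Replace the Repeated Measures ANOVA with a mixed model for the repeated scores that has a random class effect in the PEERS arm only (each control as a singleton) and small-sample degrees of freedom, alongside whatever term is used for ward.
- **Simpler option.** If classes are nested in wards, say so and use a ward-level analysis, which absorbs the class effect.

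**Cost.** One data field and some analysis wording. Confidence intervals will be wider. At classes of 6 to 8, 37 PEERS patients make only about 5 or 6 classes (37/8 = 4.6; 37/6 = 6.2), so the class variance will be imprecisely estimated and the model must be kept simple. With one ward per arm, ward cannot be separated from treatment by any model; the number of wards should therefore be stated as well.

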## Ethics statement

The studies involving human participants were reviewed and approved by Huzhou Psychiatric Hospital’s Medical Ethics Committee. The patients/participants provided their written informed consent to participate in this study.
